### Participant Selection

Children attending preschools in Mangalore Taluk aged from 24 to 72 months are included. Additional inclusion criteria are as follows: at least one soft caries lesion (ie, cavitated active caries lesion) that is small (less than half of the mesial or distal or less than one-third of the buccal, lingual, or occlusal surfaces). The exclusion criteria are pulpal exposure, history of pain, nonvital teeth, swelling or fistula, silver allergy, arrested caries or inactive lesions, teeth at the period of shedding, restored teeth, secondary caries, fluorosis, enamel hypoplasia, uncooperative behavior, physical or mental disability, and a lack of signed informed consent.

### Baseline and Follow-up Oral Examinations

Before conducting the trial, the principal investigator was trained and calibrated by experienced dental public health specialists in the Caries Assessment Spectrum and Treatment (CAST) index. Training and calibration sessions included theoretical aspects and were followed by clinical examination of a group of 10 subjects from the outpatient department. The subjects were reexamined by the principal investigator and the guide (an experienced dental public health specialist) after 1 week. The κ coefficient values for intraexaminer and interexaminer reliability were 0.88 and 0.80, respectively, reflecting a high degree of conformity in the observations.

The examinations in this study are performed by a single examiner with the help of a recording device in preschools in Mangaluru Taluk. The study sample comprises 3 groups of children aged 24 to 72 months. After baseline examination, eligible children are randomly allocated to 1 of the 3 groups using the lottery method. Group 1 receives 12% SDF semiannually, group 2 receives 30% SDF semiannually, and group 3 receives 38% SDF semiannually. Dental caries will be measured using the CAST index [9].

A CAST score of 0 is given to sound teeth (ie, with no visible evidence of a distinct carious lesion); a score of 1 for pits or fissures that are at least partially covered with a sealant material; a score of 2 for cavities that have been restored with a direct or indirect restorative material; a score of 3 for distinct visual change in the enamel only or clearly visible caries-related discoloration, with or without localized enamel breakdown; a score of 4 for internal caries-related discoloration in the dentine, with the discolored dentine visible through the enamel, which may or may not exhibit a visible localized breakdown; a score of 5 for distinct cavitation into the dentine with the pulp chamber showing intact pulp; a score of 6 for involvement of the pulp chamber with distinct cavitation reaching the pulp chamber or with the presence of only root fragments and abscess or fistula; a score of 7 for pus-containing swelling or a pus-releasing sinus tract related to a tooth with pulpal involvement; a score of 8 for teeth that have been removed because of dental caries; and a score of 9 for teeth that do not match any of the above descriptions.

All tooth surfaces, including the buccal, lingual, mesial, distal, and occlusal surfaces for posterior teeth, are evaluated for caries. Miller’s criterion is used to assess whether active caries are present; Miller’s criterion suggests that a carious lesion is termed active if a blunt University of North Carolina–15 probe can easily enter it; a carious lesion is defined as halted when the dentine cannot be penetrated.

The size of the lesion is categorized as small or large at the tooth-surface level (less than one-third of the buccal, lingual, or occlusal surface, or less than half of the mesial or distal surface).

### Intervention

#### Drug Description

The SDF in this study is Caries Stop (Biodinamica); it was used at product concentrations of 12%, 30%, and 38%. The investigators did not independently verify the concentrations stated by the manufacturer. The product is composed of fluoridric acid, silver nitrate, ammonia hydroxide and deionized water.

#### Application of SDF

Primary teeth that have cavities are separated and kept dry using cotton rollers. A plastic dish is prepared that contains 1 drop of SDF. Using a tiny brush, the SDF is administered to the carious lesion for 2 minutes. The excess is eliminated by gently wiping with another cotton pellet. The children are requested to avoid any dietary intake for an hour after application. At 6 months after the first application, a second application will be carried out. After 6 and 12 months, the principal examiner conducts a clinical examination of the teeth with a visual and tactile assessment. After a year, the efficacy of the various SDF concentrations will be evaluated.

### Outcome Measure

The primary outcome measure is caries arrest at the twelfth month of application of SDF. The secondary outcome measure is the caries increment (ie, CAST index).

### Effect Modification

A parental questionnaire is administered at baseline regarding the children’s oral hygiene habits (eg, tooth brushing), fluoride agent use (eg, fluoride toothpaste), dietary habits (eg, bottle feeding), and source of drinking water.

### Randomization and Treatment Allocation

The study is being conducted in preschools in Mangaluru Taluk. Multistage random sampling was used to select the preschools, with the following stages: (1) Mangaluru Taluk was divided into north and south zones; (2) preschools in Mangaluru Taluk were divided into government schools, government-aided private schools, and non–government-aided private schools; and (3) children were selected randomly from 437 preschools (n=218 from the south zone and n=219 from the north zone). Children were randomly allocated to 1 of the 3 groups using the lottery method. The study sample comprises 150 students aged from 24 to 72 months attending preschools in Mangaluru Taluk, including 50 students in group 1 (12% SDF semiannually), 50 students in group 2 (30% SDF semiannually), and 50 students in group 3 (38% SDF semiannually), as shown in Figure 2.

**Figure 2 figure2:**
[figure not shown]
Enrollment and allocation of sample. SDF: silver diamine fluoride.

### Random Allocation, Concealment, Masking, and Blinding

Allocation concealment was done using the sequentially numbered opaque sealed envelope method. A random code for each participant was put in an opaque package as part of a randomization system. Masking is used for the products, which are indistinguishable in terms of consistency, packaging, and labeling. The researchers applying the products are unaware of what product is being applied. A dentist’s aide opens the envelope, and the materials are then prepared after the child’s designated actions in accordance with their group allocation. The children and parents are blinded regarding their grouping. The principal examiner, who is blinded to the participating children’s group assignment, performs a clinical evaluation of the children at baseline and at semiannual follow-up exams. The dentist’s aide is unblinded to the interventions and aids in allocating the participants to the principal examiner. The participant’s allocated intervention during the trial will be revealed to the principal examiner only after the follow-up is completed.

### Sample Size Estimation

Based on the previous studies, the anticipated proportion of sound occlusal surfaces at baseline that develop into cavitated dentin lesions at the 30-month follow-up is approximately 25% [3].

Sample size calculation was performed with G* Power 3 (Heinrich-Heine-Universität Düsseldorf). Based on a 5% level of significance, power of 80%, effect size of 0.63, and 3 groups, the required sample size is 120, including 40 in each group. Considering a drop-out rate of 20%, the final sample size is 150, as shown by the following equation: final sample size = ND = N / (1 – d), where *N* is the sample size before drop-out, *d* is the expected drop-out rate, and *ND* is the sample size considering drop-out. Thus, ND = 120 / (1 – 0.2) = 120 / 0.8 = 150, and the total sample required for intervention is 150 (50 in each group). The allocation ratio is 1:1:1. The participants are allocated to the 3 groups equally.

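### The sample size rests on a rate for a different endpoint and an effect size of 0.63 with no stated metric, so 80% power is not shown for 12-month caries arrest

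*Protocol article*

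**What the plan says.** The Sample Size Estimation section opens with its only clinical planning figure: "the anticipated proportion of sound occlusal surfaces at baseline that develop into cavitated dentin lesions at the 30-month follow-up is approximately 25" per cent, taken from earlier work. It then says "Sample size calculation was performed with G* Power 3" and gives the inputs and result: "Based on a 5% level of significance, power of 80%, effect size of 0.63, and 3 groups, the required sample size is 120", with 40 in each group. Dropout of 20% is applied as "ND = 120 / (1 – 0.2) = 120 / 0.8 = 150", and "The allocation ratio is 1:1:1". The section does not name the test, the effect-size metric, the sidedness, or the outcome to which 0.63 applies.

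Elsewhere the article fixes a different target. Outcome Measure states: "The primary outcome measure is caries arrest at the twelfth month of application of SDF". Participant Selection requires at least one active cavitated lesion. Statistical Analysis models arrest as a yes/no variable at 12 months; continuous outcomes are compared across the three groups by ANOVA or Kruskal-Wallis, with post hoc tests.

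**The concern.** The planning rate and the primary outcome differ in three ways: the surface (sound v already cavitated), the event (new decay v arrest of decay) and the time (30 v 12 months). A 25% rate for the first gives no information about the second. Nothing else in the section ties 0.63 to arrest, so a reader cannot tell what difference in arrest the trial was sized to detect.

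This matters for interpretation. The Introduction hypothesises that 12% and 30% SDF will do about as well as 38%, and the Discussion expects the standard of care to change if results are as expected. If only a very large difference is detectable, a non-significant result is likely even when a lower concentration is materially worse, and it could be taken as confirming the Introduction's hypothesis.

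**Working it through.** **Inputs from the article (Sample Size Estimation):** 5% significance, 80% power, effect size 0.63, 3 groups, 40 per group, 20% dropout. **Assumed:** two-sided tests and one arrest outcome per child. All arrest rates below are assumptions, because the article gives none.

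**1. Reproducing the plan's figure.** Read 0.63 as a standardised difference between two groups (Cohen's d with the normal approximation, or Cohen's h for two proportions):

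n per group = 2 × ((1.960 + 0.842) / 0.63)² = 39.55, so 40; 3 × 40 = 120; 120 / 0.8 = 150.

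Both printed figures reproduce. The noncentral-t version gives 41 per group (123 in total), with power 0.795 at 40.

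**2. Reading 0.63 as a three-group effect size.**
- One-way ANOVA, f = 0.63: 28 in total (power 0.81), or 30 if balanced (0.84).
- Chi-square with 2 df, w = 0.63: 25 in total (0.81).

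Neither gives 120; at 120 the ANOVA power would exceed 0.999. The two-group reading therefore fits best, though the article does not confirm it.

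**3. What the two-group reading implies for a three-group test at N = 120.** Let the largest gap between arms be 0.63 SD.
- Middle arm midway: f = √(2 × 0.315² / 3) = 0.257, power 0.70.
- One arm differing from two equal arms: f = 0.63 × √2 / 3 = 0.297, power 0.83.

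These are the least and most favourable spacings. The analogue for arrest with assumed rates of 70%, 54.5% and 39% is w² = 2 × 0.155² / (3 × 0.545 × 0.455) = 0.0646; then N × w² = 7.75 on 2 df, and power is again about 0.70.

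**4. What h = 0.63 means for arrest.** With h = 2·arcsin√p₁ − 2·arcsin√p₂, a gap of 0.63 is 70% v 39%, 80% v 51%, or 50% v about 80%: roughly 30 points.

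Power for one comparison with 40 per arm is approximately Φ(h × √(40/2) − z). At h = 0.63 the first term is 0.63 × 4.472 = 2.817.

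| Two-sided alpha per comparison | z | Power |
|---|---|---|
| 5% (one comparison) | 1.960 | 0.80 |
| 2.5% (two comparisons with 38%) | 2.241 | 0.72 |
| 1.67% (all three pairs) | 2.394 | 0.66 |

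**5. Smaller differences at 40 per arm, unadjusted 5%.**

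| Assumed arrest rates | h | Power |
|---|---|---|
| 70% v 60% | 0.210 | 0.16 |
| 70% v 55% | 0.311 | 0.29 |
| 70% v 50% | 0.412 | 0.45 |
| 80% v 60% | 0.442 | 0.51 |
| 90% v 70% | 0.516 | 0.64 |

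For the three rows with a 70% reference, the pooled-variance formula for two proportions agrees to within about one percentage point.

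**The case against.** The strongest reply is that the number is right. The article never calls 0.63 an f or a w, and under an ordinary two-group reading 40 per group, 120 and 150 all follow. That stands in full. A reader might infer from the mention of three groups that only 25 to 30 children were needed and that 120 is a miscalculation. The document does not support this, because that result depends on a metric it never states.

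It can also be said that 120 may still serve a three-group test. That stands in part: power is 0.83 if one arm differs from two equal ones, but 0.70 if the middle arm lies midway.

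The adjusted powers of 0.72 and 0.66 use a correction that the article does not specify, and the choice of method may properly sit in an analysis plan. They show sensitivity and are not evidence of an error. The same holds for the powers at smaller differences: any difference below the planned one has less than the planned power, and the arrest rates are assumed.

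Finally, an article condenses, and the approved full protocol may derive 0.63 from arrest data. That would excuse silence. It does not excuse the rate that the article does print as its basis, which belongs to another endpoint.

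**Conclusion.** The point holds as a fault in the justification, not as an arithmetic error. On the article's own text, the only planning rate concerns new cavitation of sound surfaces at 30 months, whereas the trial measures arrest of active cavitated lesions at 12 months. With no metric for 0.63 and no link to arrest, 80% power for the primary outcome is not shown. On the best-fitting reading, 80% applies to a single unadjusted pairwise contrast and, if 0.63 is Cohen's h, to a gap of about 30 points. A 20-point gap has power of about 0.45 to 0.64 for the reference rates tried (70% to 90%). These sizes assume two-sided tests, one outcome per child, 40 evaluable children per arm, and arrest rates that are not in the document.

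That 120 is an arithmetic mistake, or that the trial is several times too large, should not be inferred. Nor is it established that the sponsor used Cohen's h; that is a reconstruction.

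**What to change.** Keep N = 150; the Results section reports that all 150 children are enrolled. Revise the Sample Size Estimation section as follows.

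1. Remove the 30-month sound-surface rate as the basis for the sample size.
2. State the test, sidedness and effect-size metric actually used in G*Power, keeping 0.63 on record as the planned value.
3. Restate power for 12-month arrest, labelled as a restatement with assumed rates. If the metric is Cohen's h: 40 evaluable children per arm give 80% power for one pairwise comparison at two-sided 5% to detect about 30 points (for example 70% v 39%), and about 72% if two comparisons with 38% SDF are each tested at 2.5%. If the metric is different, give the equivalent statement for it.
4. State that differences of 20 points or less are underpowered (about 45% for 70% v 50%), and that a non-significant result will be reported as an estimated difference with a 95% CI and not read as comparable efficacy.

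The cost is one rewritten paragraph and a less favourable power statement. No further children are needed, and treatment and follow-up do not change.

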### Statistical Analysis

Data analysis will be done using SPSS (version 23.0; IBM Corp). Continuous variables will be presented as the mean (SD). Categorical variables will be presented as frequencies and percentages. To confirm normality, the Shapiro-Wilk and Kolmogorov-Smirnov tests will be used. A one-way analysis of variance (ANOVA) statistical test will be used to compare the means of continuous outcome variables if the data follow a normal distribution. Nonparametric tests (ie, the Kruskal-Wallis statistical test) will be used in the data analysis in cases when there is skewed distribution of data. Post hoc tests will be performed with an ANOVA or the Kruskal-Wallis test.

Binary logistic regression will be performed. The dependent variable will be whether the lesion is arrested or not at the 12-month examination, and the independent variables will include the children’s oral hygiene habits (eg, tooth brushing), fluoride agent use (eg, fluoride toothpaste), dietary habits (eg, bottle feeding), and source of drinking water.

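### Two normality tests on the trial's own data decide how caries increment is compared, and neither resulting test adjusts for baseline caries or comes with a stated between-arm estimate and interval

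*Protocol article*

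**What the plan says.** The Outcome Measure section names two outcomes. The first is binary at lesion level: "The primary outcome measure is caries arrest at the twelfth month of application of SDF". The second is the increment: "The secondary outcome measure is the caries increment (ie, CAST index").

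The Statistical Analysis section sets a sequence for continuous outcomes:

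- Selector: "To confirm normality, the Shapiro-Wilk and Kolmogorov-Smirnov tests will be used".
- Normal branch: one-way ANOVA "will be used to compare the means of continuous outcome variables if the data follow a normal distribution".
- Skewed branch: "Nonparametric tests (ie, the Kruskal-Wallis statistical test) will be used in the data analysis in cases when there is skewed distribution of data".
- Follow-up comparisons: "Post hoc tests will be performed with an ANOVA or the Kruskal-Wallis test".

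It does not say which normality test prevails, or whether the tests are run per arm or pooled. Arrest at 12 months is handled separately, by binary logistic regression.

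Baseline caries is measured. The blinded principal examiner "performs a clinical evaluation of the children at baseline and at semiannual follow-up exams", and the Baseline and Follow-up Oral Examinations section describes CAST as a code from 0 to 9 given to teeth.

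**The concern.** A selector of this kind has three weaknesses.

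- **The target of the comparison is not fixed.** ANOVA compares means and Kruskal-Wallis compares ranks, so what the trial will have compared is unknown until the outcome data have been tested. Continuous variables are to be summarised as mean (SD) on either branch, so a rank-test p-value may stand beside means that it does not test.
- **The output does not match the question.** The Introduction expects 12% and 30% SDF to be comparable with 38%, whereas the Discussion expects 38% to be superior. Either claim needs an estimate against 38% with an interval. The planned output is an overall test and post hoc tests.
- **Baseline information is left out.** A one-way ANOVA and a Kruskal-Wallis test both have no covariate, although every child is examined for caries before treatment.

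At stake are the precision and readability of the secondary outcome. The primary outcome is not touched.

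**Working it through.** **1. Which outcome the rule governs.** Two outcomes are listed. Arrest is yes/no and has its own logistic regression. The increment is the only other one, so the rule for continuous outcomes falls on it. This is elimination, because the analysis section never names the increment.

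**2. Sample size used as input.** The Sample Size Estimation section states "power of 80%, effect size of 0.63, and 3 groups, the required sample size is 120, including 40 in each group", at a 5% level. This reproduces if 0.63 is a standardized difference between two groups:

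- n per group = 2(z₀.₉₇₅ + z₀.₈₀)² / d² = 2(1.960 + 0.842)² / 0.63² = 39.6, rounded up to 40
- 3 × 40 = 120, and 120 / (1 − 0.2) = 150

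No figure is disputed here. I use 40 per arm, the number left if 20% drop out.

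**3. Assumptions for the simulation.** The article gives no mean or dispersion for the increment. I assumed negative binomial counts per child with dispersion parameter k (smaller k means more skew). Normality was tested within each arm by Shapiro-Wilk and by Kolmogorov-Smirnov with the Lilliefors correction. ANOVA was abandoned if Shapiro-Wilk rejected in any arm.

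**4. Where the rule leads.** With means of 0.5 to 3 and k of 0.7 to 4, Shapiro-Wilk rejected in at least one arm in 100% of simulated trials, so the route was always Kruskal-Wallis. Only with larger and less dispersed counts did this weaken: with mean 6 and k = 20 it rejected in 74%.

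**5. Whether the two tests agree.** They disagreed in at least one arm in 0% of trials at mean 1, 0% to 3% at mean 2, and 7% to 56% at means 3 to 6.

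**6. Power.** Arm means were in the ratio 1 : 0.75 : 0.5, with the highest-arm mean shown below, and mean baseline caries was 4. The comparator is a log-link count model with scaled variance (quasi-Poisson F test), with arm and log(baseline + 1) as terms.

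| Highest mean, k | Baseline predictive? | Kruskal-Wallis | ANOVA | Adjusted count model |
|---|---|---|---|---|
| 1, 1.5 | yes | 34% | 40% | 53% |
| 1, 4 | yes | 52% | 58% | 62% |
| 2, 1.5 | yes | 54% | 60% | 81% |
| 2, 4 | yes | 78% | 81% | 87% |
| 1, 1.5 | no | 38% | 42% | 43% |
| 1, 4 | no | 51% | 55% | 56% |
| 2, 1.5 | no | 50% | 59% | 62% |
| 2, 4 | no | 74% | 81% | 82% |

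The gain over Kruskal-Wallis is 9 to 27 points when baseline is predictive and about 5 to 12 when it is not. In the latter case most of the gain is already present in plain ANOVA, so the larger gains come from baseline adjustment. A repeat run with a new random seed agreed within six points.

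**7. Type I error.** With no arm difference, the two-stage rule rejected in 3% to 6% of trials, within simulation error of 5%. In the four settings tabled, the adjusted model rejected in 3.7%, 6.7%, 4.0% and 4.0%, so its gain is not generally bought by a liberal test.

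**The case against.** The strongest reply is that the distribution is assumed. The article never calls the increment a count, and CAST is a tooth-level code, so the increment could be a change in score or a mean score. This stands. A reader might infer that non-normality is certain in advance, or that a negative binomial model of new surfaces with an offset for surfaces at risk is required. The documents support neither, and imposing that model would redefine the endpoint. For an ordinal change in score, which can be negative, Kruskal-Wallis is a defensible test and ANOVA is the doubtful branch.

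A second reply is that a rule written in advance is prespecified, and that if it always ends in Kruskal-Wallis the switch is inert. This also stands. A reader might infer inflated false positives or an unplanned analysis, but the rule is stated beforehand and the simulated error rate is near 5%. What remains is that the comparison is fixed only if the outcome happens to be a small count.

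Third, the normality tests do not cause baseline caries to go unused, since the ANOVA branch has no covariate either. That is right; it is a weakness of both named tests.

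Fourth, arrest might also be summarised per child, because a child can have several lesions, so the increment need not be the only target. That is possible, but no such summary is stated.

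Finally, tie-breaks and intervals often sit in an analysis plan that is not shown, and unadjusted differences in means can be recovered from the reported means and SDs. Both are fair. The selector and the two unadjusted tests are nevertheless stated choices, not gaps left by a condensed article.

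**Conclusion.** The point holds as a modest one about the secondary outcome. The article commits to a data-driven choice between two unadjusted tests for an outcome whose scale is not defined, and neither test is paired with an estimate and interval against 38% SDF.

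If the increment is a small count, the likely cost is a loss of power relative to a baseline-adjusted model, somewhere between about 5 and 27 points in the settings tried. That range rests wholly on assumed means, dispersion and baseline correlation, and shows direction more than size. There is no evidence of type I error inflation. The primary analysis of arrest is unaffected.

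**What to change.** 1. State the scale of the increment: what is counted or differenced, at tooth or surface level, and how it is combined per child.
2. Remove the normality tests as a selector of the method.
3. Prespecify one model with SDF group and baseline caries as terms. For a count of newly carious surfaces or teeth, use a log-link count model (negative binomial, or Poisson with robust or scaled variance) and report rate ratios. For a change in CAST score, use ANCOVA or an ordinal model and report the matching effect measure.
4. Report 12% vs 38% and 30% vs 38% with 95% confidence intervals.
5. Keep Kruskal-Wallis as a sensitivity check.

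The cost is analysis wording and a little more analysis work. The baseline examination is already part of the trial and the named software can fit these models, so no new data are needed. The downside is reliance on a model form, which the rank test in step 5 partly guards against. Since the article describes the trial as under way, the change should be dated before the 12-month data are examined by arm.

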### Maximum Dose and Safety Margin

The margin of safety for dosing is of paramount concern. The typical lethal dose, 50% (LD 50), for oral administration is 520 mg/kg. One drop (25 µL) contains 9.5 mg SDF and is sufficient to treat 5 teeth. The dose will be 0.95 mg/kg, and assuming that the smallest children with caries weigh between 10 kg and 15 kg, the relative safety margin for administering a whole drop to a child weighing 10 kg is therefore 380 mg/kg LD 50 / 0.95 mg/kg dosage, for a 400-fold safety margin. The actual dose will probably be much lower. One drop (25 µL) per 10 kg per treatment session is the suggested upper limit. The largest applied dose for 3 teeth is 2.37 mg, allowing for more than 400 applications [11].

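### Arrest is modelled per lesion although children are randomised; if more than one lesion per child is analysed, the planned logistic regression understates the standard error of every child-level term

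*Protocol article*

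**What the plan says.** All references are to the protocol article.

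- **Unit of randomisation.** Randomization and Treatment Allocation: "Children were randomly allocated to 1 of the 3 groups using the lottery method".
- **Unit of sizing.** Sample Size Estimation counts children: 40 per group, raised to 50 per group (150 in all) for 20% drop-out.
- **Lesions per child.** Participant Selection requires "at least one soft caries lesion (ie, cavitated active caries lesion) that is small" and sets no upper limit. In Baseline and Follow-up Oral Examinations, "All tooth surfaces, including the buccal, lingual, mesial, distal, and occlusal surfaces for posterior teeth, are evaluated for caries", and lesion size is graded per tooth surface. Application of SDF is written in the plural: "Primary teeth that have cavities are separated and kept dry using cotton rollers". Maximum Dose and Safety Margin takes one drop as enough for 5 teeth and also works an example: "The largest applied dose for 3 teeth is 2.37 mg".
- **Outcome and model.** Outcome Measure names caries arrest at 12 months as primary, without a unit. Statistical Analysis then says "Binary logistic regression will be performed" and continues "The dependent variable will be whether the lesion is arrested or not at the 12-month examination". The independent variables listed are the parental questionnaire items: oral hygiene, fluoride use, diet and source of drinking water. Treatment arm is not in the list.

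The article mentions no index lesion, per-child summary, random effect, GEE or cluster-robust variance.

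**The concern.** Lesions in one mouth share the allocated product, saliva, diet and hygiene, so their outcomes are likely to be positively correlated. A standard logistic regression with one row per lesion takes the rows as independent. It then credits the trial with more information than its children supply, and the standard error of any variable that is constant within a child comes out too small. Every listed covariate is of this kind, and so is treatment arm.

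This matters because the regression is the only named inferential method that suits a yes/no arrest outcome; ANOVA and Kruskal-Wallis are assigned to continuous variables. Confidence intervals that are too narrow would therefore fall on the primary endpoint.

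**Working it through.** **1. The plan's own sample size, to confirm its unit.** Inputs from Sample Size Estimation: 5% significance, 80% power, effect size 0.63, 20% drop-out. The type of effect size and the sidedness are not stated. Read as a two-sided comparison of two means with standardised difference 0.63:

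n per arm = 2 × (1.96 + 0.84)² / 0.63² = 15.7 / 0.397 = 39.6, so 40. Three arms give 120, and 120 / (1 − 0.2) = 150.

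The stated figures are reproduced with the child as the unit. They contain no term for several lesions per child.

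**2. Formulas for lesion-level analysis.** With m lesions in every child and within-child correlation ICC:

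- design effect DE = 1 + (m − 1) × ICC
- proportion by which the naive standard error is too small = 1 − 1/√DE
- actual error of a nominal two-sided 5% test of one contrast = 2 × [1 − Φ(1.96/√DE)]

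**3. Results.** The documents give neither m nor ICC, so both are assumptions.

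| m | ICC | DE | SE too small by | Actual error, formula | Simulated, naive | Simulated, clustered on child |
|---|---|---|---|---|---|---|
| 1 | any | 1.00 | 0% | 5.0% | – | – |
| 2 | 0.1 | 1.10 | 4.7% | 6.2% | 5.9% | 5.3% |
| 2 | 0.3 | 1.30 | 12.3% | 8.6% | 9.1% | 5.5% |
| 2 | 0.5 | 1.50 | 18.4% | 11.0% | 11.1% | 4.7% |
| 3 | 0.1 | 1.20 | 8.7% | 7.4% | 7.0% | 4.6% |
| 3 | 0.3 | 1.60 | 20.9% | 12.1% | 12.4% | 4.9% |
| 3 | 0.5 | 2.00 | 29.3% | 16.6% | 15.7% | 4.8% |
| 5 | 0.1 | 1.40 | 15.5% | 9.8% | 9.1% | 5.6% |
| 5 | 0.3 | 2.20 | 32.6% | 18.6% | 18.7% | 5.1% |
| 5 | 0.5 | 3.00 | 42.3% | 25.8% | 27.4% | 5.7% |

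The simulations used 40 children per arm, beta-binomial lesions, an assumed 60% arrest rate in all arms and 1,500 runs per setting. They tested one arm contrast, so arm was in the simulated model. At m = 3 and ICC 0.3, 120 children give 360 lesions that carry the information of 360 / 1.60 = 225.

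**4. Varying lesion counts and a 3-group test.** With unequal counts, DE = 1 + (E[m²]/E[m] − 1) × ICC. Take counts of 1 + Poisson with mean 3, so E[m²] = 2 + 9 = 11, and ICC 0.3:

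- DE = 1 + (11/3 − 1) × 0.3 = 1.80
- one contrast: 2 × [1 − Φ(1.96/√1.80)] = about 14%
- 3-group test (2 df): 0.05^(1/1.80) = about 19%

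A simulation of this case with 4,000 runs gave 14.7% and 19.0%; a second one with 1,500 runs gave 12.8% for one contrast. Across the settings in the table but with varying counts, the naive error was 7.3% to 28.5%, and the clustered error 3.9% to 6.9%.

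**The case against.** The strongest reply is that lesion-level rows are inferred. The dependent variable is worded in the singular, the sample size counts children, and one outcome per child is a possible reading with no inflation at all. Several exclusions concern single teeth or lesions, so it is unclear how many lesions per child would be analysed. The tooth numbers in the dose section are illustrations, not expected counts. This stands as a limit on how firmly the error can be sized. It does not settle the matter, because nothing in the article states one lesion per child or says how that lesion would be chosen.

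A second reply is that this is a condensed article, and that naming binary logistic regression does not rule out a clustered version set out in an analysis plan that is not shown. That is fair for the choice of correlation structure. But the article itself fixes a lesion-level outcome and a model family for child-randomised data, and that pairing needs correcting where it is written.

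A reader might infer three stronger things that the text does not support:

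- That the plan, as written, would declare false differences between concentrations too often. Arm is not a listed term, so this follows only once arm is entered. The wording of the list leaves room for that.
- That the habit covariates suffer most. Arm is equally a child-level factor, and no lesion-level covariate is listed for contrast.
- That every cavitated tooth is treated and analysed. Application of SDF uses the plural but does not say all.

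**Conclusion.** The concern holds conditionally. The article sets a lesion-level dependent variable against child-level randomisation and sizing, and states nothing that would make the lesions independent or account for their dependence. If more than one lesion per child is analysed, standard errors are too small for every child-level term: the listed habit covariates as written, and the arm effect once arm is in the model.

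Under a fixed 2 to 5 lesions per child and ICC 0.1 to 0.5, standard errors are about 5% to 42% too small and a nominal 5% single-contrast test runs at about 6% to 26%. Varying counts or a 3-group test push this higher. The size rests wholly on these assumed values. The direction rests only on positive within-child correlation and more than one lesion per child. The point should be settled before the 12-month data are analysed.

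**What to change.** In Statistical Analysis, state the unit of the arrest outcome and replace the model sentence by one of these:

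1. **Keep all lesions.** Use logistic GEE with child as cluster and robust standard errors, or a mixed logistic model with a child random intercept. Enter treatment arm as a factor. Report the proportion of lesions arrested per child as a sensitivity analysis.
2. **One index lesion per child.** Define it before treatment by a stated rule and keep ordinary logistic regression, again with arm as a factor.

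Option 1 costs one sentence of wording and a child identifier on each lesion record. It can be run in SPSS 23 and needs no extra children. Its intervals will be wider than the naive ones, which is the correction intended. Option 2 is simpler but leaves the remaining lesions out of the main analysis.
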